**e. Study duration:**

The total duration of the study is 12 weeks – this includes a period of hospital based treatment followed by a post recovery period. The Ayurvedic drug will be prescribed as per protocol for a total duration of 12 weeks.

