**l. Laboratory investigations:**

These are common to the each of the three Ayurveda formulation drug trials:

1. Haemogram, Platelet count, Total leukocyte differential count, Hemoglobin and ESR,
2. Liver function test - Serum Bilirubin, ALT, AST, Alkaline phosphatase,
3. Kidney Function Test ( Serum creatinine, Blood Urea Nitrogen)
4. Lipid profile (Total cholesterol, HDL cholesterol, LDL cholesterol, Triglycerides, VLDL)
5. Blood Sugar Level
6. Urine Routine
7. C-Reactive protein titer
8. LDH, Ferritin
9. Pro-Cal
10. CK, B-type natriuretic peptide (BNP), Troponin, D-Dimer
11. Serum Electrolytes (Sodium, Potassium, Chloride, Iron, Zinc, Manganese) Vitamin D, B12
12. Oxidation Biomarkers-Superoxide Dismutase (SOD), Glutathoine (GSH)
13. Cytokine Panel (Interleukin-2, Interleukin l - 4, Interleukin-6, Interleukin-10, TNF-α, Interleukin-1β, Interleukin-13), Monocyte Chemotactic Protein (MCP), Gamma Interferon. RATIONALE FOR CYTOKINE ASSAY: Cytokine assay can be used to study important anti-viral effects (gamma interferon), immune mediated inflammation (IL-6, anti-TNF, IL-17), TH 1 and TH 2 immune response and antibody producing B cell activity (IL4, IL13), activation of immune cells such as macrophage activation (MCP). Intense up regulation and elevation of IL 6 and several other cytokines has been reported by several clinical case series and research in COVID-19 and can guide specific therapy (as in case of use of monoclonal antibody to IL-6 receptor being used to treat Cytokine storm in COVID 19)
14. Serum Immune Response tests (IgG and IgM) for COVID-19
15. Urine Pregnancy Test for women of child bearing potential

Other Investigations:

1. USG Abdomen and Pelvis
2. Color Doppler and 12 Lead ECG
3. Chest X-ray
4. HRCT Chest

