# 8. STUDY DURATION, FOLLOW- UP SCHEDULE AND PROCEDURES

This is summarized in Figure 1 and Table 1. There are several foot notes provided in Table 1 to further clarify a particular event/test procedure and often with particular reference to the role of the study investigator. Several of the clinical events with reference to clinical examination, study record forms and questionnaires, study procedures, laboratory diagnostics and assessments are elaborated in Appendices enclosed with the protocol (Appendix A to S).

It should be noted that this is a study treatment protocol and that the time to outcome in terms of recovery following onset of illness and/or admission to hospital is a varying parameter. The large majority of study patients are expected to recover completely but based on prior knowledge the mortality of COVID-19 in severe case in well documented (see literature review, section above). It is expected that the majority of patients will recover and be discharged to home within 5 days to 15 days of hospitalization.

However, all study patients who recover are required to follow with the study investigators on pre-determined time points as shown in Table 1.

The total duration of the study is 12 weeks and includes the duration of treatment and post clinical recovery or post-hospital discharge period to ensure optimum recovery and regain of health status.

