# 13. LABORATORY & OTHER INVESTIGATIONS

These are common to the each of the three Ayurveda formulation drug trials:

1. Blood/Serum (routine): Haemogram, Platelet count, Total leukocyte differential count, Hemoglobin and ESR, Blood sugar level (Fasting), Liver function test and Liver Enzymes (SGOT,SGPT, Alkaline Phosphatase), Renal functions (Serum creatinine, Blood Urea Nitrogen), Lipid profile (Total cholesterol, HDL cholesterol, LDL cholesterol, Triglycerides, VLDL)
2. Serum (inflammatory markers, organ damage):C-Reactive protein titer, lactate dehydrogenase, ferritin, Pro-Calcitonin, Troponin, D-Dimer,
3. Special tests: Blood for Vitamin D, Vitamin B12, Oxidation Biomarkers (Superoxide Dismutase (SOD), Glutathoine (GSH)
4. Cytokine Panel: Interleukin (IL) IL-2, IL-1 beta, IL-4, IL-6,IL-10, IL-13, IL-17, TNF-α, Monocyte Chemotactic Protein-1 (MCP), Interferon gamma, TGF-bet
5. Serum Protective Antibody Response: IgM and IgG against SARS-CoV-2
6. Routine Urinalysis, Urine Pregnancy Test for women of child bearing potential
7. Confirmatory Diagnostic Test: Nasal and/or Throat swab for real time RT-PCR for SARS-CoV-2 (See Appendix O)
8. Other Investigations: USG Abdomen and Pelvis, ECHO-Color Doppler and 12 Lead ECG

Chest X-ray, HRCT scan Chest

**13.1** Rationale for Cytokine Assay: Cytokine assay can be used to study important anti-viral effects (gamma interferon), immune mediated inflammation (IL-6, anti-TNF, IL-17), TH 1 and TH 2 immune response and antibody producing B cell activity (Il 4, IL 13), activation of immune cells such as macrophage activation (MCP). Intense up regulation and elevation of IL 6 and several other cytokines has been reported by several clinical case series and research in COVID-19 and can guide specific therapy (as in case of use of monoclonal antibody to IL-6 receptor being used to treat Cytokine storm in COVID 19).

Detail methods for diagnostic tests, serology and cytokine assay are described in Appendix O.

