# APPENDIX

## Appendix A: Schedule of Events

**Table 1: SCHEDULE OF EVENTS:**

| VISIT | Baseline | D 4 | Day 4 Discharge | Discharge | Week 4 | Week 8 | Week 12 | Remarks |
| --- | --- | --- | --- | --- | --- | --- | --- | --- |
| Informed Consent,  Selection Criteria, Demographics, Disease Features, Baseline Symptoms | X |  |  |  |  |  |  |  |
| Medical History and Comprehensive Physical Examination | X |  |  | X |  | X | X |  |
| Symptom, Vital Parameters | X |  |  |  |  |  |  |  |
| Adverse Events **^a^** |  | X | X | X | X | X | X | X |
| AyurvedicEvaluation**^b^** | X |  | X |  | X | X | X |  |
| Pulse Oximetry**^c^** | X | X | X | X | X | X | X |  |
| USG Abdomen and Pelvis | X |  |  |  |  |  |  |  |
| Color Doppler and 12 Lead ECG | X |  |  | X |  |  |  |  |
| Chest X-ray | X | X | X | X |  |  |  |  |
| HRCT Chest | X | X |  | X |  |  |  |  |
| Pregnancy Test | X |  |  |  |  |  |  |  |

| VISIT | Baseline | Day 4 | Day 4- Discharge | Discharge | Week 4 | Week 8 | Week 12 | Remarks |
| --- | --- | --- | --- | --- | --- | --- | --- | --- |
| Hb, TLC, DLC, Platelet, Urine ®**^d^** | X |  | X |  | X | X | X |  |
| ESR and CRP**^e^** | X |  | X |  | X | X | X |  |
| LFT, BUN, SrCreatinine**^f^** | X |  | X |  | X | X | X |  |
| Lipid Profile | X |  |  |  | X |  | X |  |
| LDH, Ferritin**^g^** | X |  | X |  | X |  | X |  |
| IL-6 Pro-cal**^h^** | X |  | X |  | X |  | X |  |
| CK, BNP, Troponin,  D-Dimer **^i^** | X |  | X |  | X |  | X |  |
| Na, K, Cl, Fe, Zn, Mn, Vitamin D , B12 | X |  |  | X |  |  | X |  |
| Oxidation Biomarkers  -SOD, GSH | X | X |  | X |  |  | X |  |
| Cytokine Panel**^J^** | X |  |  | X |  |  | X |  |
| Serum Immune Response**^k^** | X | X | X | X | X | X | X |  |
| Health Related-Behaviour Fitness (HR-BHF) VAS questionnaire, Self Reported Questionnaire (Mobile app)**^L^** | X | X | X | X | X | X | X |  |
| Dispense study medication**^m^** | X |  |  |  |  |  |  |  |
| Completion report |  |  |  | X |  |  | X |  |

Footnotes:

1. Symptom Assessment, vital parameters and monitoring of adverse events to be performed daily by Physician
2. Daily Ayurvedic Monitoring till discharge by Ayurvedic Physician and subsequently for 4, 8 and 12 week.
3. Pulse oximetry to be performed daily

d-f: These tests should be performed at Baseline and once in 3 days till discharge and in addition as per discretion of the treating physician

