## Appendix E: Yashtimadhu ([*Glycyrrhiza glabra*](https://www.sciencedirect.com/topics/pharmacology-toxicology-and-pharmaceutical-science/glycyrrhiza-glabra)) – A Research Update

SARS-CoV-2 is an envelope, positive-sense, single-stranded RNA β-corona virus and shown similarity with severe acute respiratory syndrome (SARS) and Middle East respiratory syndrome (MERS) viruses. Since its origin, scientists and physicians are making efforts to understand its entry and pathogenicity, and the most notable findings regarding its entry into host revealed out, where several SARS-CoV-2 enters into cells through binding of its spike proteins with host cell receptors, angiotensin-converting enzyme 2 (ACE2) and leads to down regulation of the ACE2 receptor. This leads to viral entry and replication, as well as severe lung injury. The occurrence of COVID-19 elevated intense attention not only within India but internationally. Therefore, there is an urgent need for its management and prevention.

[*Glycyrrhiza glabra*](https://www.sciencedirect.com/topics/pharmacology-toxicology-and-pharmaceutical-science/glycyrrhiza-glabra) (family Fabaceae), commonly known as [licorice](https://www.sciencedirect.com/topics/pharmacology-toxicology-and-pharmaceutical-science/liquorice), one of the important an herbaceous perennial Ayurvedic medicinal has been used as a [flavoring agent](https://www.sciencedirect.com/topics/pharmacology-toxicology-and-pharmaceutical-science/flavoring-agent) in foods and medicinal remedies for thousands of years. Licorice root has been widely used around the world to treat cough since ancient times. It contains active compounds, including glycyrrhizin, glycyrrhetinic acid, [flavonoids](https://www.sciencedirect.com/topics/pharmacology-toxicology-and-pharmaceutical-science/flavonoids), [isoflavonoids](https://www.sciencedirect.com/topics/pharmacology-toxicology-and-pharmaceutical-science/isoflavonoids), and [chalcones](https://www.sciencedirect.com/topics/pharmacology-toxicology-and-pharmaceutical-science/chalcone-derivative). Glycyrrhizin and glycyrrhetinic acid are considered to be the main active components and are potent inhibitors of [cortisol](https://www.sciencedirect.com/topics/pharmacology-toxicology-and-pharmaceutical-science/hydrocortisone) metabolism, due to their steroid-like structures. The root of this plant has been used for cough, colds, asthma, and COPD (Ram et al., 2011).

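### No sodium or potassium test is scheduled between hospital discharge and week 12 of Yashtimadhu dosing, and the protocol's laboratory lists disagree on electrolytes

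*Combined protocol and SAP*

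**What the plan says.** Three places list the laboratory tests, and they do not match.

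- **Synopsis, item l** includes "Serum Electrolytes (Sodium, Potassium, Chloride, Iron, Zinc, Manganese) Vitamin D, B12" without timing.
- **Section 13** names no sodium, potassium or chloride. Its routine bloods include "Renal functions (Serum creatinine, Blood Urea Nitrogen), Lipid profile", and it keeps the vitamins that share the synopsis line: "Special tests: Blood for Vitamin D, Vitamin B12, Oxidation Biomarkers".
- **Appendix A, Table 1** has the row "Na, K, Cl, Fe, Zn, Mn, Vitamin D , B12", marked at baseline, discharge and week 12. The row carries no footnote letter. The row "LFT, BUN, SrCreatinine" is marked at weeks 4 and 8 as well.

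The section on clinical evaluation says that laboratory and imaging tests follow Table 1. Sections 15.5 and 15.6 give only a generic laboratory entry for weeks 4 and 8.

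On exposure, the synopsis states: "The Ayurvedic drug will be prescribed as per protocol for a total duration of 12 weeks". Section 3.1 allows the Ayurveda clinician to raise the daily number of tablets and ties no laboratory test to that change. Section 8 expects that "the majority of patients will recover and be discharged to home within 5 days to 15 days of hospitalization".

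On the drug, Appendix E states: "Glycyrrhizin and glycyrrhetinic acid are considered to be the main active components and are potent inhibitors of" cortisol metabolism, and it attributes this to their resemblance to steroids.

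**The concern.** Safety is part of the primary objective (Section 4), and Section 18.3 bases safety assessment partly on laboratory tests. The protocol itself credits Yashtimadhu with a steroid-like action on cortisol metabolism. Yet sodium and potassium are the chemistry tests left unmarked at weeks 4 and 8, in the middle of outpatient dosing, although renal and liver chemistry is drawn at both visits. A disturbance that arose after discharge and resolved before week 12 would have no scheduled measurement in either arm. About 70 patients, one arm of the Yashtimadhu trial, would be exposed.

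The link from cortisol metabolism to electrolytes is an assumption of this review. Appendix E names no effect on sodium, potassium or fluid balance.

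**Working it through.** The plan states no figure to reproduce. The check is a reading of the schedule plus simple arithmetic.

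**Step 1: the rows of Table 1 side by side**

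| Test | Baseline | Day 4 to discharge | Discharge | Week 4 | Week 8 | Week 12 |
|---|---|---|---|---|---|---|
| Sodium, potassium, chloride (with trace elements and vitamins) | X | – | X | – | – | X |
| Liver tests, urea nitrogen, creatinine | X | X | – | X | X | X |

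Footnotes d to f and g to i extend other rows, j covers cytokines and k covers serology. None adds an electrolyte test.

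**Step 2: which list governs.** The clinical evaluation section makes Table 1 the rule for laboratory testing, and Sections 8 and 15 also point to it. Section 13 also lacks CK and BNP, which Table 1 schedules. It therefore reads as an incomplete list, not as a decision to drop electrolytes.

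**Step 3: the interval without a scheduled test**

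Inputs: 12 weeks = 84 days of dosing (synopsis e); discharge at day 5 to 15 for most patients (Section 8); day count from admission (Section 5). The calculation assumes that dosing starts at about admission.

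- Discharge at day 15: 84 − 15 = 69 days; 69/84 = 82%.
- Discharge at day 5: 84 − 5 = 79 days; 79/84 = 94%.

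Sensitivity:

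- With the week 12 visit moved by the 5-day window of Section 19.10, the interval runs from 79 − 15 = 64 to 89 − 5 = 84 days.
- The clinical evaluation section allows for recovery at 3 to 4 weeks. Discharge at day 21 to 28 gives 84 − 28 = 56 to 84 − 21 = 63 days (67% to 75%).
- The rule that merges week 4 or week 8 with a nearby discharge does not shorten the gap, because neither visit carries the test.

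**Step 4: the interval if sodium and potassium were added at weeks 4 and 8 (days 28 and 56)**

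- Discharge before day 14: the longest gap is 56 − 28 = 84 − 56 = 28 days.
- Discharge from day 14, if that counts as within two weeks of week 4: week 4 merges into discharge and the next test is at day 56. The longest gap is then at most 56 − 14 = 42 days, and 41 days for discharge at day 15.

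**The case against.** The strongest reply is that the patient is not unobserved.

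- Note (i) to Table 1 lets the treating physician order any test at any time.
- Section 15 lists vital parameters and adverse event monitoring at weeks 4, 8 and 12, and the daily app asks about suspected side effects and alerts the investigator.
- Withdrawn patients have completion laboratory tests if possible.
- A DSMB reviews adverse events.
- Sodium and potassium are measured in both arms at the end of 12 weeks, so a disturbance that persists would be seen.
- Appendix E calls the aqueous extract safe and non-toxic, although it gives no electrolyte data there.

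All of this stands, and it limits the point to tests that are not scheduled. It does not supply a planned between-arm measurement during outpatient dosing. Whether discretionary tests would be ordered unevenly between arms cannot be settled from the documents, and the point does not need it.

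A reader might infer more than the documents support:

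- **That a site following Section 13 would never test electrolytes.** Table 1 governs and requires them three times.
- **That the third stop rule in Section 14 could not operate.** It also acts on an adverse clinical profile.
- **That a report of no electrolyte signal would mean only that nobody looked.** The discharge and week 12 values are real data in both arms.
- **That an electrolyte hazard is documented.** The documents describe an action on cortisol metabolism and stop there.

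**Conclusion.** The point holds in limited form. The three laboratory lists disagree on electrolytes. The governing schedule leaves 69 to 79 of 84 dosing days (82% to 94%) without a scheduled sodium or potassium test for patients discharged at day 5 to 15, and fewer for later discharge. What could be missed is a transient mid-course disturbance; a lasting one would appear at week 12.

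This rests on three assumptions: dosing starts at about admission, Table 1 is followed as written, and an action on cortisol metabolism could affect electrolytes. The last is not stated in the documents. The schedule is common to all three drug trials, and only the pharmacological reason is particular to Yashtimadhu. This is an inexpensive improvement to the safety data and does not undermine the trial.

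**What to change.** 1. Reconcile synopsis item l, Section 13, Sections 15.5 and 15.6 and Table 1 on electrolytes, and check the result against the description of the drug in Appendix E.
2. As a data-collection change for the safety objective, separate sodium and potassium from the trace-element and vitamin row. Run them in both arms on the blood already drawn at weeks 4 and 8, at least in the Yashtimadhu trial. The longest scheduled gap then falls from 69–79 days to 28 days, or to 41–42 days where discharge at day 14 or 15 absorbs the week 4 visit.

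The cost is two assays on existing samples at two existing visits, plus a schedule amendment with ethics committee review. No extra visit or blood draw is needed. No dose, stopping or treatment rule is proposed.

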**A.** **Sanshamani Vati Plus (SV +):**

The proposed study includes a combination of *Tinospora cordifolia* (Guduchi) and *Piper longum* (Pippali) as one of the Ayurvedic formulations*.* Both these botanicals are very well studied and documented for their anti-viral, anti-inflammatory and immunomodulatory potential (Rasayana). The details of ingredients and related research are annexed as Appendix C.

The ingredients are used in Ayurveda practice for various indications including respiratory (*Shvasa, Kasa, Jvara*) and infectious diseases (45). This particular combination has been described in the treatment of ‘*Vata Kapha Pradhana Sannipatika Jwara’* (VKJ) which shares symptomatology similar to COVID-19. The proposed formulation is indicated in the VKJ, as described in Ashtanga Hridaya (a text of 8^th^ century, which is referred as one of the three important Ayurveda classics known as ‘*Brihadtrayee’*)

कफवाते .. पिप्पलीचूर्णयुक्तोवाक्वाथछिन्नोद्भवोद्भवा (अष्टांगहृदयज्वरचिकित्सा६०)

Sanshamani Vati Plus is a dried aqueous extract of *Tinospora cordifoila* (TC) used to treat VKJ and immunocompromised conditions in various disorders. Both the botanicals are abundantly available in the Indian sub-continent. Its immune modulating function has been effectively used in treatment of HIV and Chikungunya (46, 47). The clinical profile of COVID-19 is similar to the Ayurvedic description of VKJ and ‘Shvasa Kasa Jwara’ and thus the stated formulation has a potential to treat COVID-19. While TC will target the immune system, Pippali will improve the respiratory component. The advisory by the AYUSH Ministry for COVID-19 has also recommended *Sanshamani Vati* for improving immunity (48).

Dosage: *Samshamani Vati* Plus will be given as two tablets (each containing 300 mg aqueous extracts of *Tinospora cordifolia* and 75 mg aqueous extracts of *Piper longum*) twice daily with warm water. However, the Ayurveda clinician can increase the dose (up to four tablets per day) considering the symptoms, dosha dominance and patient’s need. In such a case the attending Ayurveda physician will document every change in dose everyday with its reason.

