# 15. STUDY PROCEDURES: TIMELINES AND EVENTS SCHEDULE

The overview is shown in Table 1.

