15.1 Baseline Visit: (Visit 1)

Patients who meet the criteria for selection, must have the following procedures completed during this visit prior to study entry.

Visit 1 (Baseline)

|  | Providing with Patient Information Fact Sheet for thorough study. |
| --- | --- |
|  | Signing of Informed Consent. |
|  | Complete medical examination form: medical history, comprehensive physical examination, co-morbidity, medication history. |
|  | Symptom Assessment, Vital Parameters |
|  | Record Baseline Symptoms |
|  | Comprehensive Ayurvedic evaluation. |
|  | Laboratory work up- general health and advanced test and cytokines as in Appendix O |
|  | Ultrasound abdomen and Pelvis, Chest X-ray, HRCT chest, |
|  | Colour Doppler and 12 Lead ECG |
|  | Pulse Oximetry |
|  | Health Related-Behaviour Fitness (HR-BHF) VAS questionnaire, Self-Reported Questionnaire (Mobile app) |
|  | Dispense study medication and begin medication log entry |

15.2 Visit 2 (Day 4):

|  | Symptom Assessment, Vital Parameters |
| --- | --- |
|  | Brief Ayurvedic Evaluation |
|  | Health Related-Behaviour Fitness (HR-BHF) VAS questionnaire, Self-Reported Questionnaire (Mobile app) |
|  | Laboratory work up |
|  | Chest X-ray, HRCT chest, |
|  | Pulse Oximetry |
|  | Monitor Adverse Events |

15.3Visit 2 (Day5 up to-Discharge) (Daily Assessment):

|  | Symptom Assessment, Vital Parameters |
| --- | --- |
|  | Brief Ayurvedic Evaluation |
|  | Laboratory work up |
|  | Pulse Oximetry |
|  | Monitor Adverse Events |
|  | Colour Doppler, ECG |
|  | Chest X-ray, and HRCT chest |
|  | Health Related-Behaviour Fitness (HR-BHF) VAS questionnaire, Self-Reported Questionnaire (Mobile app) |
|  | Completion and Outcome Report |

15.4DISCHARGE

|  | Symptom Assessment, Vital Parameters |
| --- | --- |
|  | Brief Ayurvedic Evaluation |
|  | Laboratory work up |
|  | Pulse Oximetry |
|  | Monitor Adverse Events |
|  | Colour Doppler, ECG |
|  | Chest X-ray, and HRCT chest |
|  | Health Related-Behavior Fitness (HR-BHF) VAS questionnaire, Self-Reported Questionnaire (Mobile app) |
|  | Completion and Outcome Report |

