15.5. Visit 4 (week 4)

|  | Symptom Assessment, Vital Parameters |
| --- | --- |
|  | Brief Ayurvedic Evaluation |
|  | Laboratory work up |
|  | Pulse Oximetry |
|  | Monitor Adverse Events |
|  | Health Related-Behaviour Fitness (HR-BHF) VAS questionnaire, Self-Reported Questionnaire (Mobile app) |
|  | Drug Compliance, Dispense study medication |

15.6 .Visit 5 (week 8)

|  | Symptom Assessment, Vital Parameters |
| --- | --- |
|  | Comprehensive Ayurvedic Evaluation |
|  | Medical History, Comprehensive Physical examination |
|  | Laboratory work up |
|  | Pulse Oximetry |
|  | Monitor Adverse Events |
|  | Health Related-Behaviour Fitness (HR-BHF) VAS questionnaire, Self-Reported Questionnaire (Mobile app) |
|  | Drug Compliance, Dispense study medication |
|  |  |

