# 16. INVESTIGATIONAL DRUGS AND DOSING

The investigational drugs to be used individually in 3 separate drug trials of 2 arms each in this protocol are Sanshamani Vati Plus, AYUSH 64 and *Glycyrrhiza glabra*. The dosage schedule for each one of them is as follows:

i) AYUSH-64: 500 mg tablet, 2 tablets bid (twice daily)

ii) Yashtimadhu: 300 mg tablet, 2 tablets bid (twice daily)

iii) Sanshamani Vati Plus: Each tablet to contain 300 mg Guduchi plus 75 mg Pippali, 2 tablets bid (twice daily) with warm water.

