g-iThese tests should be performed at Baseline and once in 3 day till discharge, week 4 and week 12 and in addition as per discretion of the treating physician

j Cytokine Panel includes IL-2, Il-4, IL-6, IL-10, TNF-α, IL-1β, IL-13, MCP, Gamma Interferon, to be performed at Baseline, Day 5, Day 10, Day 15

Day 20/Discharge, Week 8, Week 12.

k. Serum Immune Response includes IgG, IgM, and will be performed at Baseline, Day 2, Day 4, Day 6, Discharge, Week 4, Week 8, and Week 12.

L .Health Related -Behaviour Habit Fitness , HR-BHF, WHO-QOL Bref, Mobile Application for recording COVID-19 symptoms daily

m. Study medication will be dispensed every 4 weeks, at baseline, week 4 and week 12

Note:

i)The treating physician can ask for any investigations anytime, if need arises and as per clinical judgement

ii)If the discharge takes place within 2 weeks of a particular timeline (week 4 or week 8) then the events/investigations for that particular timeline will merge with those required at time of discharge (DO NOT repeat again for that timeline)

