## Appendix C: Sanshamani Vati Plus: Ingredients and Related Research

**Background**

Although the rationale is included in the protocol document, a detailed information about research on Ayurveda formulations are discussed in following sections.

The Medanta Hospital in Delhi has implemented a traditional formulation of Ashtang Sangraha (SanshamaniVati Plus) in a state-of-the-art super-specialty hospital. The SanshamaniVati is dried aqueous extract of *Tinosporacordifoila* (TC) indicated in VKJ and immunocompromised conditions. Its immune modulating function has been effectively used HIV and chikungunya (1,2). The advisory by the AYUSH Ministry for COVID-19 has also recommended *SanshamaniVati* [equivalent of 200 ml decoction of *Tinosporacordifolia* and 4 grams *Piper longum* powder / day orally] for improving immunity (3). SamshamaniVati Plus is a formulation made up of aqueous extract of *Tinosporacordifolia* (TC) and fine powder of *Piper longum* (PL). This combination is specific to VKSJ and is mentioned in Ashtanga Hrudaya. This has been selected as therapeutic intervention considering its specificity to the clinical picture of COVID-19, the known immune-enhancing effect of TC and effects of PL in respiratory system. *SamshamaniVati* will be given as 500 mg. thrice daily with warm water for 2-3 weeks.

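### Table 1 footnote m and Appendix C contradict the 12-week drug course in the synopsis and the week 0, 4 and 8 dispensing in Section 15

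*Combined protocol and SAP*

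**What the plan says.** The length of the drug course is stated outright once, in Synopsis e: "The Ayurvedic drug will be prescribed as per protocol for a total duration of 12 weeks". Sections 5 and 8 give 12 weeks as the length of the study, and the three dose lines in Section 16 carry no duration.

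**Dispensing.** Section 15.1 has, at baseline, "Dispense study medication and begin medication log entry". Sections 15.5 (week 4) and 15.6 (week 8) carry the same entry: "Drug Compliance, Dispense study medication". Section 15.7 (week 12) lists compliance and the completion report, but no dispensing. In Table 1 of Appendix A the dispensing row is ticked at baseline only, and its footnote m reads "Study medication will be dispensed every 4 weeks, at baseline, week 4 and week 12". Section 15 introduces that table with "The overview is shown in Table 1".

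**Regimen for Samshamani Vati Plus.** Section 16 states: "Each tablet to contain 300 mg Guduchi plus 75 mg Pippali, 2 tablets bid (twice daily) with warm water". Synopsis k and Section 3.1 A agree on two tablets twice daily, and Section 3.1 A adds that "the Ayurveda clinician can increase the dose (up to four tablets per day) considering the symptoms". The background text of Appendix C says that Samshamani Vati "will be given as 500 mg. thrice daily with warm water for 2-3 weeks".

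**Follow-up wording.** The section on clinical evaluation including Ayurvedic assessment places the end of treatment at discharge and treats the assessments at weeks 4, 8 and 12 as coming after treatment. Section 9 also describes the Table 1 follow-up as a post-treatment schedule.

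**The concern.** A site can find different answers to two simple questions: when to hand out drug, and for how long a patient takes it. Footnote m concerns all three trials; the Appendix C sentence concerns only the Samshamani Vati Plus trial.

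If some sites work from footnote m and others from Section 15, drug-arm patients at week 12 would be a mixture of on-drug and off-drug. The week-12 laboratory, quality-of-life and safety comparisons would then estimate something that depends on which page a site read. Drug handed out at week 12 would also be taken after the last scheduled visit, with no later safety visit.

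An Appendix C course has an earlier effect. It would stop treatment within the period over which time to clinical recovery is measured, and the patient could not literally satisfy the intent-to-treat condition in Section 17.2.

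**Working it through.** **Inputs.** Course length: 12 x 7 = 84 days (Synopsis e). Standard dose: 4 tablets a day, each 300 + 75 = 375 mg (Section 16). Primary time frame: up to 28 days (Section 11.1). Visit window: 3-5 days either side (Section 19.10). The size of a hand-out is not stated; 28 days is assumed because it matches the four-week interval.

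**Step 1. Days supplied, visits on schedule.**

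| Source | Hand-outs that fall before day 84 | Days supplied | Days not supplied |
|---|---|---|---|
| Section 15 | weeks 0, 4, 8 | 3 x 28 = 84 | 0 |
| Footnote m | weeks 0, 4 | 2 x 28 = 56 | 84 - 56 = 28 (28/84 = 33%) |

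Section 15 therefore reproduces the 12-week course when every visit is on its nominal day. Under footnote m the unsupplied days are 57-84, and one hand-out of 4 x 28 = 112 tablets is issued at the final visit.

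The gap depends on the assumed quantity. With s days per hand-out it is 84 - 2s: 28 days at s = 28, 18 days (18/84 = 21%) at s = 33, and none at s = 42. For sites that follow Section 15, footnote m adds no gap.

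**Step 2. Position against the primary outcome.** The first unsupplied day under footnote m is day 57, after the 28-day time frame. The primary outcome is unaffected.

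**Step 3. Appendix C against Section 16.**

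- Daily mass: 3 x 500 = 1500 mg against 4 x 375 = 1500 mg. These are equal if 500 mg means total tablet mass.
- Frequency: three times against twice daily. One 500 mg dose is 500/375 = 1.33 tablets, so it cannot be given with whole study tablets.
- Duration: 14-21 days against 84, that is 14/84 = 17% to 21/84 = 25% of the course.
- Shortfall against the four weeks of intervention in Section 17.2: 28 - 21 = 7 to 28 - 14 = 14 days. The same subtraction gives the part of the 28-day primary window spent off drug.

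**Step 4. Whether Section 15 is complete.** Two provisions show that it is not.

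- *Window.* A week-4 visit may fall on day 28 + 5 = 33. With a 28-day hand-out, 33 - 28 = 5 days are uncovered.
- *Merged visits.* Note ii under Table 1 merges the week-4 or week-8 events into discharge when discharge is within two weeks of that visit, so for week 4 from day 28 - 14 = 14. Section 8 expects most discharges after 5 to 15 days, so some patients will qualify. The discharge list in Section 15.4 has no dispensing item, and Figure 1 says to skip the evaluation. If nothing is dispensed at discharge, the next hand-out is at week 8: 56 - 28 = 28 days uncovered. If dispensing moves to discharge with the merged visit, there is no such gap.

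**The case against.** The strongest reply is that footnote m corrects itself. Its four-weekly interval already implies week 8, Section 15.6 orders dispensing then, Section 15.7 orders none at week 12, and Table 1 is described as an overview. The baseline-only tick is weak evidence on its own, because other rows are also ticked loosely: symptoms and vital signs are ticked at baseline only although their footnote asks for daily assessment. All this makes a slip for week 8 the likely explanation, and most sites would probably do the right thing.

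It does not make the footnote harmless. The clinical evaluation section ties the success of the trial to strict compliance with Table 1, Section 8 says that the table's footnotes are there to clarify procedures, and Section 18.1 bars deviations outside emergencies.

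On Appendix C, the reply is that it is a research background, that its sentence omits the word Plus, and that three dosing statements agree against it. That lowers the chance that anyone doses from it. But the sentence is an instruction, stands under the Sanshamani Vati Plus title, and directly follows the text that selects that combination. Because the dose lines give no duration, it is also the only duration attached to this formulation.

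Four stronger readings are tempting and are not supported:

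- *A reader might infer that Section 15 leaves no gap at all.* The visit window and the merged-visit rule show otherwise.
- *A reader might infer that only footnote m and Appendix C are out of line.* The clinical evaluation section also fits poorly with a 12-week course.
- *A reader might infer that Appendix C changes the daily amount.* On total tablet mass it does not.
- *A reader might infer that larger hand-outs are needed.* The documents do not state the quantity per hand-out, and removing the contradictions does not require fixing one.

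**Conclusion.** The contradictions are real and minor. Footnote m, followed literally with 28-day hand-outs, supplies 56 of 84 days and issues drug at the last visit. The gap shrinks with larger hand-outs, and footnote m causes none at sites that follow Section 15. It bears on week-12 secondary and safety data, not on the 28-day primary outcome.

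The Appendix C sentence, if followed, replaces an 84-day course with 14-21 days in one of the three trials. That ends treatment 7-14 days before the primary window closes and falls equally short of the Section 17.2 condition. Its daily mass of 1500 mg matches Section 16, assuming that 500 mg refers to both ingredients together. If it meant the Guduchi extract alone, the comparison would be 1500 mg against 4 x 300 = 1200 mg.

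Neither point affects the sample size or the significance level. How many sites would follow the conflicting texts cannot be known from the documents, so the figures describe a literal reading and are not a forecast.

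**What to change.** 1. **Table 1, dispensing row:** tick baseline, week 4 and week 8.
2. **Footnote m:** replace week 12 by week 8.
3. **Appendix C:** change the regimen sentence to *two tablets twice daily with warm water for 12 weeks*.
4. **Section 16:** add *for 12 weeks* to each of the three dose lines.
5. **Clinical evaluation section:** reword so that it is hospital treatment, not the study drug, that ends at discharge, and so that weeks 4, 8 and 12 are follow-up visits.
6. **Note ii under Table 1:** state that when a week-4 or week-8 visit is merged with discharge, the drug due at that visit is dispensed at discharge.

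The cost is wording only: two ticks, one footnote, one appendix sentence, three dose lines, one reworded description and one added rule. No new visit, data field or extra tablets are needed. Section 19.9 requires ethics committee agreement for protocol changes, so these edits should go together in one amendment.
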